### Participants

Eligibility criteria include: 1) currently practicing physician (M.D. or D.O.), 2) at least 18 years of age, 3) willing and able to attend the six-week intervention, 4) fluent in English, 5) access to the internet and email, and 6) score of four or greater on the four-item Perceived Stress Scale [PSS-4; 70]. Perceived stress will be assessed using the PSS-4 during the initial phone screening. Exclusion criteria include: 1) having a current and consistent meditation practice (i.e., engaging in a formal meditation practice at least three days per week for five minutes each day), 2) previous participation in a Four Immeasurable course (e.g., attending a Brahmaviharas meditation retreat), 3) regular tobacco use (given its impact on immune function; [70]). Eligibility is intentionally broad to enhance generalizability to the physician population. We do not exclude participants on the basis of medical or psychiatric conditions or medication use. We do, however, assess these characteristics at baseline. Participants report current medication use (including dosage, frequency, and reason for use) and provide information on any diagnosed psychiatric conditions, use of mental health services, and the frequency of such use. These data are collected to characterize the sample and are available for use in sensitivity or exploratory analyses.

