*Mid-Course Assessment (T2).* At the halfway point of the intervention (week 3), all participants will be emailed a link to complete self-report questionnaires assessing only the primary outcome and the mediator variables. The reduced midpoint battery takes approximately 5–10 minutes to complete.

*Post-Intervention Assessment (T3).* All participants will be emailed the post-intervention assessment link and mailed a second blood collection kit to complete both tasks within 2 weeks following the conclusion of the study intervention. The questionnaire will include all study variables. Assessment burden at post-intervention is equivalent to baseline (approximately 20–30 minutes for questionnaires and 10 minutes for blood collection).

*Procedure for Blood Collection, Processing, and Storage.* The Tasso T-20 device [73] will be used to collect, store, and transport capillary blood for testing at the Social Genomics Core Laboratory. The Tasso is designed for use in non-clinical settings with adult populations. After collection, samples will be stored at −20 °C and analyzed in a single batch once data collection is complete.

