#### Primary outcome: Stress.

Stress will be assessed using the ten-item Perceived Stress Scale (PSS) [80]. The PSS will be administered at baseline (T1), mid-course (T2), and post-intervention (T3). The PSS evaluates how often individuals appraised situations in their lives as stressful during the past month. Respondents respond on a five-point Likert scale from 0 (never) to 4 (very often). All scores are summed to provide a total stress score. Scores range from 0 to 40, with higher scores indicating greater perceived stress. The PSS has been widely used with healthcare provider populations [81,82] and has been shown to be responsive to MBIs [83].

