As a complementary, pre-specified sensitivity analysis under a missing-at-random assumption, a linear mixed model will be fit using all available data from all randomized participants with at least one post-baseline observation, with fixed effects for condition and time (categorical) and a random intercept for participants. The between-condition contrast at the post-intervention endpoint will be extracted from this model to correspond to the primary estimand, and change over time and the condition-by-time interaction will be examined as secondary, descriptive analyses [136,137]. As an additional sensitivity analysis, we will repeat the primary outcome models using a per-protocol approach, restricting to participants in the BEST condition who attended at least three of the six intervention sessions (and the corresponding WLC participants), to assess whether the intervention effect differs among those who received the intervention as intended. Since a per-protocol analysis does not preserve the original randomization, it will be interpreted as a complementary, exploratory analysis rather than a confirmatory test of the ITT result. Lastly, because the analyzable sample is modest, the trial is not powered for formal moderation or subgroup analyses. Any examination of whether intervention effects differ across physician subgroups (e.g., specialty) will be exploratory and hypothesis-generating, intended to inform future adequately powered trials rather than to provide confirmatory tests. All tests, primary and secondary outcomes, will be two-sided with an alpha level of 0.05. All analyses will be conducted in R version 4.4.3 [71].

*Mediation analyses.* Mediation analyses will be conducted using the PROCESS macro in R [138]. To enhance the temporal precedence of the intervention’s effect on perceived stress through each mediator, we will assess the outcome (perceived stress) and mediators (compassion, positive emotions, equanimity/mindfulness) for all participants at the midpoint of the six-week intervention (T2). We will fit a parallel mediation model that includes group assignment (BEST vs. WLC) at T1 as the predictor variable, compassion, positive emotions, and equanimity/mindfulness at T2 as the mediators, and PSS scores at T3 as the outcome. The model will control for T1 perceived stress and for each mediator’s T1 values.

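### The sensitivity mixed model names only a random intercept, a restrictive covariance for three PSS visits, so the standard error of its T3 contrast may be wrong in either direction (minor)

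*Protocol article*

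**What the plan says.** The model is introduced in the Data analysis plan (primary and secondary outcomes): "As a complementary, pre-specified sensitivity analysis under a missing-at-random assumption, a linear mixed model will be fit". It is specified "with fixed effects for condition and time (categorical) and a random intercept for participants". On the quantity to be reported: "The between-condition contrast at the post-intervention endpoint will be extracted from this model to correspond to the primary estimand". The interaction appears only afterwards: "change over time and the condition-by-time interaction will be examined as secondary, descriptive analyses". The article ties no other residual structure and no robust SE to this model. Robust standard errors are mentioned once, in the descriptive-analyses paragraph, as a general remedy for non-normality.

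Three features of the design bear on the covariance of the PSS:

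- **Recall window** (Primary outcome: Stress): "The PSS evaluates how often individuals appraised situations in their lives as stressful during the past month".
- **Visit timing** (Procedures and study flow): T1 falls in the two weeks before the first class. For T2, "At the halfway point of the intervention (week 3), all participants will be emailed a link to complete self-report questionnaires". T3 falls in the two weeks after the six-week course.
- **Selection on stress** (Participants): entry requires a "score of four or greater on the four-item Perceived Stress Scale".

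The Sample size section gives one PSS correlation, 0.50 between baseline and post-intervention. No PSS SD is given for any visit.

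**The concern.** A random intercept with independent, equal-variance residuals is compound symmetry: Var(T1) = Var(T2) = Var(T3), and the same correlation for T1-T2, T2-T3 and T1-T3. The design gives reasons to doubt both parts.

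- **Correlation.** Taking T2 at the end of week 3, adjacent visits are about 3-5 weeks apart, so past-month windows overlap by roughly 0-9 days. T1 and T3 are at least about six weeks apart and share no recall days. T1-T3 is therefore plausibly the least correlated pair, yet the model replaces its correlation with a pooled one.
- **Variance.** Screening on PSS-4 near T1 can narrow the spread at T1, which may widen again by T3. A floor effect after the course could do the opposite.

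The model exists to check the confirmatory PSS result under missing at random. If its SE depends on a covariance restriction that has nothing to do with missingness, closer or weaker agreement with the ANCOVA cannot be read cleanly as robustness or fragility.

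**Working it through.** **The plan's own figure.** The article gives a figure only for the ANCOVA. With N = 72, one covariate, α = 0.05 and power 0.80, the noncentral F gives f = 0.335. Then d = 2f√(1 − r²) = 2 × 0.335 × √0.75 = 0.58, which reproduces the stated value. No figure is given for the mixed model.

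**Inputs.** From the article: 45 per arm, about 72 of 90 with T3 data, T1-T3 r = 0.50, two-sided α = 0.05. Assumed, because the article does not give them: adjacent correlations (T1-T2/T2-T3) from 0.60/0.60 to 0.65/0.70, and SDs at T1/T2/T3 in three patterns: equal; 0.93/0.97/1 (T1 7% below T3); 1/0.95/0.85 (T3 15% below T1). The model is given a condition-by-time term, since otherwise it has no T3 contrast.

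**Formulas (complete data, n per arm).** The compound-symmetry fit uses s² = mean of the three variances and ρ = mean covariance / s².

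- Plain T3 difference, baseline free: reported variance (2/n)s², true variance (2/n)σ₃². SE ratio = s/σ₃.
- T3 difference with baseline means constrained equal: reported variance (2/n)s²(1 − ρ²), true variance (2/n)(σ₃² − 2ρσ₁₃ + ρ²σ₁²).
- Type I error ≈ 2[1 − Φ(1.96 × SE ratio)].

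**Worked cases.**

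1. Equal SDs, adjacent 0.60/0.60, baseline constrained: ρ = (0.60 + 0.60 + 0.50)/3 = 0.567. Reported 1 − 0.321 = 0.679; true 1 − 0.567 + 0.321 = 0.754. Ratio √(0.679/0.754) = 0.949.
2. Plain T3 difference, equal SDs: s = σ₃, ratio 1.00 whatever the correlations.
3. Plain T3 difference, SDs 0.93/0.97/1: s² = (0.865 + 0.941 + 1)/3 = 0.935, ratio 0.967.
4. Plain T3 difference, SDs 1/0.95/0.85: s² = (1 + 0.9025 + 0.7225)/3 = 0.875, ratio 0.935/0.85 = 1.10.

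**With 18 of 90 missing T3 at random** (large-sample compound-symmetry fit against the sandwich SE):

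| SDs T1/T2/T3 | Adjacent r | Baseline constrained: SE ratio (type I) | Plain T3 difference: SE ratio (type I) |
|---|---|---|---|
| 1/1/1 | 0.60/0.60 | 0.950 (6.3%) | 0.996 (5.1%) |
| 1/1/1 | 0.65/0.65 | 0.919 (7.2%) | 0.994 (5.1%) |
| 1/1/1 | 0.65/0.70 | 0.908 (7.5%) | 0.996 (5.1%) |
| 0.93/0.97/1 | 0.60/0.60 | 0.919 (7.2%) | 0.961 (6.0%) |
| 0.93/0.97/1 | 0.65/0.70 | 0.881 (8.4%) | 0.961 (6.0%) |
| 1/0.95/0.85 | 0.60/0.60 | 1.037 (4.2%) | 1.102 (3.1%) |
| 1/0.95/0.85 | 0.65/0.70 | 0.985 (5.4%) | 1.102 (3.1%) |

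**Baseline as a covariate, T2 and T3 as outcomes** (equal SDs, complete data, visit-specific slopes). The residual variances are 1 − r₁₂² at T2 and 1 − 0.25 = 0.75 at T3. For r₁₂ = 0.60: √[((0.64 + 0.75)/2)/0.75] = 0.963. For r₁₂ = 0.65: √[((0.5775 + 0.75)/2)/0.75] = 0.941. The SE is 4-6% too small.

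**Is the 7% pattern plausible?** Suppose 10-30% are screened out and PSS-4 correlates 0.75/0.60/0.50 with T1/T2/T3 (all assumed). The SDs become 0.915/0.947/0.963 to 0.845/0.904/0.934, so T1 is 5-10% below T3.

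**Model exactly as listed** (condition and time, no interaction): the SE ratio is 1.00, but the coefficient averages the condition difference over all three visits, baseline included. It is not a T3 contrast.

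**The case against.** A reader might infer that the design makes the visits unequal and that the T3 SE is therefore too small. The documents do not support that. They give no SD by visit and only one correlation, so inequality is plausible but not shown. The direction depends on how the contrast is built and on whether the T3 SD lies above or below the pooled SD. For a plain T3 difference with equal SDs there is essentially no error, and a falling SD makes the SE too large. The recall overlap is short, and at the wider spacings it vanishes, so the adjacent correlations used here are assumptions. All of this stands, and it is why the point is put in both directions.

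It can also be said that the larger SE errors need a condition-by-time term and a baseline constraint that the sentence does not list. That is true. However, the contrast is meant to match a baseline-adjusted estimand, and the same section says all outcome models adjust for covariates, so a version that uses baseline is the closest reading. With baseline as a covariate the unequal-correlation argument falls away, but unequal residual variance remains (4-6%).

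Residual structure is often left to a fuller plan, and one is registered on OSF but not shown; it may say more. Naming a random intercept does not strictly exclude other residual terms. The article does, however, state a covariance choice, and as written it is the restrictive one.

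Finally, this is a complementary analysis with no decision rule attached. That stands too and limits the weight of the point.

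**Conclusion.** The point holds as a minor improvement. The stated structure is more restrictive than three fixed visits require, and the SE of the T3 contrast may be off by several percent in either direction. Under the assumptions above, it is about 5-9% too small with baseline constrained and equal SDs, and about 8-12% too small if the T1 SD is 7% below the T3 SD. For a plain T3 difference it is about right with equal SDs, about 4% too small in the second pattern and about 10% too large if the T3 SD is 15% below the T1 SD. Bias in the point estimate is negligible (under 0.01 SD in a rough calculation).

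Nothing here touches the confirmatory result, which is the T3 ANCOVA with multiple imputation. Secondary outcomes are measured only at T1 and T3, so for them only the equal-variance restriction is in question. The missing interaction in the listed fixed effects is a separate fault in the same sentence; it matters here only because no T3 contrast exists without it.

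**What to change.** In the mixed-model sentence of the Data analysis plan, replace the random intercept with an unstructured within-participant covariance across T1, T2 and T3 (T1 and T3 for secondary outcomes). Fit it by REML with Kenward-Roger or Satterthwaite degrees of freedom, and list condition-by-time among the fixed effects so that the T3 contrast is defined. Heterogeneous compound symmetry can be named as the fallback if the model does not converge. If the registered plan already specifies such a structure, the article's sentence should be brought into line with it.

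Cost: one sentence and a small change in the R code. An unstructured 3 × 3 covariance has six parameters against two for compound symmetry, so four more for the PSS (one more for two-visit outcomes), with a small loss of degrees of freedom at about 90 participants. By the article's account outcome data are not accessed for analysis until collection ends, so the change can be recorded as a dated amendment before then.

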### Data management and monitoring

Data will be collected using Qualtrics, with access restricted to the principal investigators. This limited access heightens data security, minimizes data entry errors, and maintains study integrity. Additionally, participant confidentiality will be maintained by using de-identified data in Qualtrics. Given the low risk of serious adverse events and the limited follow-up window, a data monitoring committee (DMC) will not be utilized. The principal investigators, in collaboration with the IRB, will oversee the trial and ensure participant safety.

## Discussion

To our knowledge, this is the first trial to test the effects of a mindfulness intervention that includes all four components of the traditional Four Immeasurables practice. Findings from this trial will provide unique and valuable insights into the impact of a novel mindfulness intervention for an at-risk group of individuals who currently lack effective, widely available, and scalable practices to address the stress inherent to their occupation. If effective, results may suggest the utility of the BEST intervention for other stressed populations beyond healthcare providers.

From a traditional Buddhist perspective, cultivating the Four Immeasurables is an essential step toward liberation, or the ultimate goal of freedom from suffering [55]. The virtues of loving-kindness, compassion, sympathetic joy, and equanimity are in the spirit of benefiting others, fostering a mind inclined towards love, and counteracting feelings of anger, hatred, envy, attachment, and aversion [55]. From a psychological perspective, kindness, compassion, joy, and equanimity fall under the broader construct of positive emotional states, which have been shown to be associated with beneficial mental and physical health outcomes [140–144]. Given the importance of the emotional states cultivated through the Four Immeasurables practice from both traditional and psychological perspectives, and the common characteristics shared across the three highly prevalent symptoms of working in high-stress healthcare environments, namely reduced empathic concern and low positive affectivity, the Four Immeasurables practice may be uniquely positioned to support this at-risk group.

This study has several strengths, including the use of both subjective and objective measures of intervention effects, a randomized design, and institutional support to facilitate trial success. Several limitations should also be considered. First, this is an open-label trial. Given the nature of a mindfulness intervention, participants and intervention instructors cannot be blinded to condition [72,145,146], and participants are aware they are enrolled in a study of a meditation program, which may influence their responses to self-report measures. This concern is compounded by the use of a waitlist rather than an attention- or expectancy-matched active control. Since expectancy is not equalized across arms, intervention participants may anticipate benefit in a way waitlist participants do not, potentially inflating self-reported outcomes, a recognized limitation of waitlist-controlled designs. These expectancy and self-report biases are somewhat mitigated by our objective, inflammation-based outcome, which is more difficult for participants to influence than self-report measures.

A related limitation concerns allocation concealment. Because the principal investigator conducts eligibility screening, informed consent, and baseline assessment while also holding the master randomization list, allocation is not concealed through personnel separation. However, the randomization sequence was generated before enrollment, so individual assignments were fixed in advance and could not be altered. Therefore, concealment relied on adherence to the pre-specified procedure of not consulting assignments until after baseline completion, supported by predefined, largely objective eligibility criteria that limit the potential for foreknowledge to influence enrollment.

The principal investigator also conducts the analyses unblinded to allocation. Although an independent, blinded analyst was not feasible given the size and structure of the trial, this risk is mitigated by preregistering all primary and secondary outcomes and the analysis plan (ClinicalTrials.gov, NCT07283744, and OSF, osf.io/npcax), which constrains analytic flexibility. Analyses will adhere to the preregistered plan, and any deviations will be explicitly identified and justified.

Additionally, the trial’s sample size is also constrained by recruitment capacity, with an anticipated enrolled sample of 90 and projected attrition of approximately 19% [126]. The study is powered to detect a moderate between-group effect (*d* = 0.58), consistent with those typically observed for digitally delivered mindfulness-based interventions [124], but may not detect smaller true effects. Findings should therefore be interpreted as informative about moderate-magnitude effects rather than as definitive tests of smaller ones.

More broadly, our intervention targets individual-level psychological processes, whereas the literature on physician well-being consistently identifies organizational and structural factors—including workload, administrative and clerical burden, electronic health record demands, and scheduling—as major drivers of stress and burnout. BEST is not designed to modify these systemic factors, and our findings should be interpreted accordingly. Should the intervention demonstrate benefits, these effects should be understood as individual-level coping resources that complement, rather than substitute for, organizational efforts to improve provider well-being, and should not be taken to imply that responsibility for addressing burnout rests solely with physicians. Conversely, limited or null effects may reflect constraints imposed by an individual-level approach on organizationally generated stressors rather than the ineffectiveness of the practices themselves. We view individual- and organizational-level approaches as complementary and necessary components of a comprehensive strategy for physician well-being.

Finally, the optional post-intervention feedback form is completed only by intervention-arm participants who choose to respond. These data may therefore reflect self-selection and may not be representative of all participants. We treat these qualitative responses as exploratory rather than as a representative account of intervention acceptability.

### Dissemination

Findings from this trial will be disseminated through peer-reviewed journal manuscripts, academic conferences, and meetings with local, state, and national hospital administrators.

## Conclusion

In summary, this trial not only aims to reduce distress and enhance well-being in a vulnerable population but also to provide valuable empirical evidence to the growing body of literature on the utility of traditional meditative practices in contemporary settings. The intervention as a combined package is a relatively unexplored topic ripe for important scientific discoveries that could add to the burgeoning evidence base of positive psychological interventions.
